## C.2. Development of data collection instruments

Draft data collection instruments for the first submission of this proposal were developed based on various forms from several previous field studies in Zimbabwe, Tanzania and more recently from our study on SODIS in

Bangladesh and in Bolivia. Final drafts of these instruments in English are currently developed incorporating findings of the 2002 study (Appendix F-2). These instruments will be submitted for IRB clearance at all study sites before their use in this trial. However, actual interviews are performed using the instruments written in local Quechua language (previous versions from 2001 in Appendix J). They were translated into the local Quechua language and back-translated to English to ensure accuracy of the translation and clarity of contents. They include a screening and enrolment questionnaire and five principal data collection instruments: i) a questionnaire for baseline assessment of socio-demographic characteristics of the study child and household including questions on water management and use; ii) a weekly observational protocol to monitor water, hygiene or sanitary conditions at the community and in the household; iii) a weekly follow-up questionnaire on gastrointestinal symptoms to be administered by the community-based field staff; iv) a questionnaire for assessing exposure risks at four different times during the study period; v) We also developed an illustrated household morbidity diary for self-administration and recording of diarrheal illness for the study child and household members. This serves to validate our weekly diarrheal morbidity assessment through a maternal interview. Similar participatory instruments have been successfully used previously (Stanton and Clemens 1987) and their validity and use in the application of diarrheal disease research has been advocated recently (Goldman et al. 1998, Kalter et al. 1991). A similar tool has also been successfully applied by our group in a recent study on gastrointestinal illness in HIV population in the US (Colford et al. Appendix G). These instruments have been shown to be at the same time appropriate for the use by locally trained personnel and capable of measuring the outcomes and exposures of interest. Questionnaires were developed using English templates from previous studies and were then discussed with the local Bolivian field team. Interviewers and data collectors were trained during a one-week workshop organized locally. Overall, our pilot study and previous experience demonstrated that with adequate personnel and with the instruments that we developed, data collection was complete, operationally and logistically feasible to obtain in a rural setting and over a prolonged period of time.

### C.3. Study site and choice of study design

Study area and population: The trial will be conducted in Totora, a section of the province of Carrasco, one of the 16 provinces in the department of Cochabamba. The capital of this region is the city of Totora (approx. 1600 habitants). The communities involved in this project are situated in a radius of about 30 km around the city of Totora. These communities have an estimated total population of 13,000. They are situated in an area that is unsuitable for well sinking or gravity water supplies. About 20% of the rural population are children <5 years and 28.5% are 5-14 years old. The average family size is 4. The incidence of diarrhea in children <5 years of age is estimated from different national studies at 4-5 episodes/child/year. (S.N.S.I.)(Prado and O'Ryan 1994, Quick et al. 1999).

The SODIS Program in Bolivia: The SODIS diffusion program has been developed since 1997 through a number of experimental field studies on the efficacy and acceptability of SODIS in Sacabamba (CdA 1997). The SODIS Foundation and later in 1999 the Centro de Aguas y Saneamiento Ambiental and developed different educational materials such as videos, tapes with tales for children, flip charts for community awareness raising and booklets for household distribution (Appendix I) and radio broadcasts. PCI, one of the partners in the SODIS Network Bolivia, took active part in distributing the materials and introducing SODIS as part of their program on “*salud integral*”. (See section B.5).

The Bolivian SODIS Program was launched with initial funding from the World Bank which is supporting the production of dissemination materials, and an award obtained at the Second World Water Forum, The Hague ([name], 2000). Full funding for the entire Latin American SODIS Program was received in Jan 2001 (Appendix B). Our proposed trial will be conducted within the area of operation of PCI /Cochabamba, one of the partners in the SODIS network. PCI is introducing SODIS in groups of communities continuously over a period of 24 months through trained technicians and community field workers and teachers. PCI is expanding its activities within the area of Totora and has agreed to collaborate with this project allowing a staggered, community-based introduction of the SODIS method. PCI provides us, thus, with the framework to adopt a “stepped-wedge design” for our community randomized controlled trial, where the intervention is introduced step-wise (Kirkwood et al. 1997, Smith and Morrow 1991).

### C.4. Research team and network of collaborators

The proposed trial represents a substantial multi-disciplinary effort by teams from Switzerland, Bolivia, and the United States with well-defined roles based on each group's specific expertise in the design, conduct, and analysis of the project. The team from UC Berkeley has extensive field experience resulting from the design and management of the four federally funded large-scale drinking water intervention trials described in Section C1. Each of these trials is targeted to a different population (elderly, HIV-infected, or segments of random populations with no

immunocompromised). These separate studies are being conducted in Walnut Creek (immunocompetent population), San Francisco (HIV positive participants), and Sonoma (elderly participants), California as well as in Davenport, Iowa (immunocompetent participants from the challenged water source on the Mississippi River). The first of these studies (PILOTWET in Walnut Creek) is in press (Appendix G) and was released early by the journal on its web site to permit inclusion in an upcoming report to Congress (<http://www.cdc.gov/ncidod/eid/vol8no1/colford.htm>).

The Swiss team has a longstanding experience in applied public health research in developing countries. Members of our team have conducted various randomized controlled trial in the SPf66 malaria vaccine development (Acosta et al. 1999, Alonso et al. 1998, Alonso et al. 1994), the effectiveness of impregnated bednets (Binka et al. 1996, Lengeler and Snow 1996), and lately the effects of co-artemeter in the treatment of schistosomiasis (Utzinger et al. 2000a). Diarrheal disease research and health impact evaluations of water and sanitation interventions studies in Burkina Faso, Cote d'Ivoire, Chad, China, Bangladesh and Zimbabwe, constitute another major field of the group's expertise (Booth et al. 1996a, Booth et al. 1996b, Cissé et al. 1999, Gagneux et al. 1999, Hobbins et al. 2000b, Mausezahl et al. 1996, Pitts et al. 1996, Shier et al. 1996, Tanner et al. 1993, Utzinger et al. 1999, Utzinger et al. 2000b).

The Bolivian group at the University San Simon (UMSS): Since a preparatory visit of the PI/STI in 2003 the Bolivian group is newly composed of the Centro de Centro de Aguas y Saneamiento Ambiental (CASA) at the technical faculty, the Centro de Estadística Aplicada (CESA), a biostatistics support unit within UMSS, and the Laboratories for Medical Diagnostic (LABIMED) of the Faculty of Medicine.

*The Centro de Aguas y Saneamiento Ambiental* has a reputation in local water research and water quality monitoring of ground and waste water in the region and the evaluation of water quality of mobile water providers in the peri-urban areas of Cochabamba, (CdA 1999). Their work focuses on the removal of iron and manganese from groundwater for drinking purposes, the monitoring of heavy metal existence in the Ichilo and Caine rivers. Since 1996 their research has been on appropriate technologies for solar disinfection of drinking water (Brofferio 2000) and on the health effects of pesticides in soil and water.

*The Centre for Applied Statistics (CESA)* is a unit developed by the programme of University Institutional Cooperation between UMSS and three Belgian Universities. CESA supports the UMSS faculties in planning the research activities and in analyzing and treating the data. The Faculties of Sciences and Technologies, of Medicine and of Agronomy of the UMSS are participating at the first phase of the project. CESA has two missions: i) training in biostatistics and research design and data management, and ii) statistical support to research activities within the UMSS.

*Laboratories for Medical Diagnostic (LABIMED)* is an operating unit of the Institute for Biomedical Investigations and Social Interactions (IIBISMED) of the Faculty of Medicine. The LABIMED laboratories were created in 1990 with the scope of providing the Faculty with high quality diagnostic laboratory services, facilitating teaching and scientific research. LABIMED is a regional reference laboratory.

## C.5. Institutional support and approval

A number of different institutions are involved in the conduct of this study. The letters of support and approval letters from the relevant institutions (Swiss Tropical Institute, University of San Simon, PCI, Cochabamba) involved are found in Appendix K. The status of approvals for the protocol as of July 2003 is as follows;

- i.) approved by the Berkeley Committee for the Protection of Human Subject, OHRP IRB number 00000775 (February 27th 2003)
- ii.) approved by the Swiss ethical research board in Basel (Ethikkommission Beider Basel) OHRP IRB number 00003565 (March 11th 2003), Annual Ethical Review on March 14th 2004
- iii.) approved by the University of San Simon IRB, Bolivia OHRP IRB number 00003509 on April 19, 2004
- iv.) The protocol and has been read and approved by local partner institutions including the Fundación SODIS and Project Concern International (PCI)/Bolivia and will next be presented to the local government at the Municipality of Totora District. The letters of institutional clearances are attached (Appendix C).

## D. Research Design and Methods

### D.1. Overview of the design

The principal aim of the proposed study is to evaluate the ability of a simple, low-cost, home-based water treatment method based on solar disinfection to reduce gastrointestinal illness among children less than 5 years of age in rural Bolivian communities. To achieve this objective we will conduct a pair-matched, cluster-randomized controlled trial following equal numbers of children in each of 22 villages (Appendix L). The intervention to be tested is a method called SODIS (Solar Disinfection) which makes use of the synergistic effects of solar radiation and thermal heating from sunlight. The SODIS Program, by design, disseminates the intervention to whole communities, rather than to individual households or single individuals. The major steps in the randomization process are:

1. 22 villages (from a total of 60 possible villages) will be selected for enrollment from the Totora District;
2. each village will be paired with another village with a similar incidence of baseline diarrhea, as suggested by the reviewer previously;
3. within each pair of villages, one village will be randomly selected for the “treatment” arm and one village for the “control” arm.
4. within each village all families will receive the SODIS intervention. A random sample of 30 children under 5 years of age will be enrolled in the study (total of 330 children in each arm of the study, 660 children total for the study). In families with multiple children the youngest child will be enrolled.

Please note that study introduces no delay into the receipt of SODIS by the control villages because control arm communities will receive the SODIS intervention at the end of the trial according to the scheduled implementation plans of the SODIS Program.

The 660 children (all <5 years old at enrollment), will be followed and monitored for the occurrence of diarrheal diseases over a period of 12 months. Data on diarrheal illness will be obtained from daily morbidity diaries kept by mothers/caretakers (\*) and through weekly home visits by our project staff. Participating mothers/caretakers of participating children will be interviewed at baseline and repeatedly during the trial with regard to current water management, behavioral and environmental exposures of their child in the household and the community surroundings.

(\* Note: the closest caretaker of the child will be contacted as respondent only if the team cannot locate the mother after two unsuccessful visits to the home)

Stool samples will be collected from a random sample of 220 children during the baseline morbidity surveys. The same children will be asked to provide two more samples at the time of their first symptomatic diarrheal episode and after 6 months follow-up. Testing of the stool specimen will be done at LABIMED, University of San Simon (UMSS)/Medical Faculty.

Systematic monitoring of the water quality of raw water sources used for drinking water and of household water samples after treatment with the SODIS device will be conducted. Testing for fecal coliform contamination will be done using portable equipment. More sophisticated analyses for bacteriophages and parasites (*Cryptosporidium* and *G. lamblia*) will be done at the laboratories of the Centro de Aguas y Saneamiento Ambiental/UMSS.

## D.2. Inclusion criteria

Subjects: Families with children <5 eligible for the study are eligible to participate if they:

- i) live permanently in the village;
- ii) consistently use unprotected drinking water sources;
- iii) give informed consent;
- iv) Children <5 years must be permanently living with their family. In households with more than one child <5 years all the children will be enrolled.

Village clusters are selected from village profiles available from PCI. They apply the following criteria to include communities within the SODIS Program:

- i) the village has no treated or improved individual- or functioning communal improved water supplies ;
- ii) the village anticipates no drinking water interventions other than those of the Latin American SODIS program (as documented by village water and sanitation development plans and discussion with the municipality or other NGOs;
- iii) uniform support for study participation is expressed by the village leadership.

## D.3. Informed Consent

The informed consent process is based on IRB-approved procedures for the international SPf66 malaria vaccine trials (Alonso et al. 1994). We have provided a detailed outline of procedures and a letter of consent which we have already piloted (Appendix M, see also Section E.). If the mother of the child is willing and eligible to participate the project staff will go through the consent form with the mother. The consent form will contain all information about the design of the study, activities involved when participating and potential risks and benefits. Signatures of both parents and all household members living permanently there will be required. If the parents agree to participate and have signed the informed consent form the enrollment questionnaire will be filled out at the participant's home (Appendix J). If consent forms cannot be completed during the first visit field staff will arrange for follow-up meetings. The closest caretaker of the child will be respondent only if the team cannot locate the mother after two unsuccessful visits to the home.

## D.4. Definition of diarrhea (principal outcome)

An episode of diarrhea will be defined in this activity and throughout the trial as a 24 hours period with three or more non-bloody loose or liquid motions, or one or more bloody, loose or liquid motions and three diarrhea-free days between a new onset. This is in concordance with the WHO recommendations and recent research (Ahmed et al. 1994, Aziz et al. 1990, Morris et al. 1994) and allows the comparison with other studies on diarrheal diseases in developing countries. Concepts of diarrheal illness and disease differ within and between cultures (Pitts et al. 1996, Weiss 1988). For example, a nutritional program in Honduras neglected to use word 'empacho' in their instructions for correct feeding practices of diarrheal cases. The subsequent inclusion of the folk term significantly improved the program's impact (Scrimshaw and Hurtado 1988). Attempts will be made during the pilot phase to assess the cultural perception of diarrheal illness and to elucidate the folk terminology and basic local illness beliefs about diarrhea (Appendix L). We conducted similar studies in previous research to obtain and validate local folk terms for diarrheal illness that resemble most closely the biomedical definition for diarrheal illness mentioned previously (Mausezahl 1996, Pitts et al. 1996).

A start of a new episode of diarrhea will be defined as the first day of diarrhea that occurs after at least three consecutive diarrhea-free days. Similarly, the end of an episode is determined by the onset of three consecutive diarrhea-free days. Our choice of three rather than some other number of disease-free days is based on the work of Morris *et al* who modelled the sensitivity of different definitions of diarrheal episodes and described the definition we

have chosen as ideal in situations of medium to high incidence (specifically greater than six trigger events/child/year) allowing for different lengths of duration and within-child clustering (Morris et al. 1994). Persistent diarrhea is defined as an episode lasting longer than 14 days according to WHO standards (Anonymous 1988); diarrhea episodes of shorter duration will be defined as "acute".

## D.5. Evaluation of the outcome measures

Evaluation of differences in the primary outcome measure between the active and control arms will be through relative incidence rates of gastrointestinal illness (total episodes of child diarrhea / total person-time of observation in the control group divided by the same measure in the active group) adjusted for the nature of the cluster sampling. Secondary outcomes include child-level outcome measures such as the total number of days with diarrhea, the mean duration of diarrhea, and the number of visits to health care providers caused by the diarrhea. We also will obtain information to allow an analysis using a combination of symptoms that describe 'highly credible gastrointestinal illness' (HCGI) (Payment et al. 1991) from our weekly diarrhea monitoring household interviews (Appendix J).

Outcome data will be collected through a surveillance system established to measure diarrheal morbidity through daily illness diaries kept by the mother/caretakers of the children, and through weekly home-visits by project staff. A standardized questionnaire will be administered covering the clinical signs and gastrointestinal symptoms of current illness. Environmental (household and village-specific characteristics) as well as behavioral traits (water and food handling practices in the home, presence of pets, latrine arrangements) will also be recorded. Weekly home visits result in a total of 52 environmental and morbidity recording sheets for each child in the study.

Stool specimens will be collected and submitted for microbiologic analysis from a sub-sample of 220 (33%) of the children in the study during baseline, at their first diarrheal episode. In addition, as suggested by the reviewer, the entire sub sample will also be re-examined at a fixed time (at 6 months of follow up). This will allow us to measure three additional pathogen-specific outcomes: the prevalence of asymptomatic infections; the proportion of diarrhea attributable to infection for each organism detected in the study; and differential (pathogen-specific) infection rates in intervention and control group.

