#### **D.6. c. Determining the monthly incidence of child diarrhea in both arms of the study**

This task will be achieved by monitoring diarrheal morbidity in a cohort of 30 study children (from different households) in each of the 22 village-clusters, (total of 330 children in each study arm, 660 children total). We will obtain information on our main outcome, cluster(village)-level incidence rates of diarrheal episodes through two monitoring procedures for the entire 12 month follow-up period:

- 1.) Morbidity diaries: Morbidity calendars will be kept by mothers/caretakers of the children. The use of morbidity diaries or 'illness calendars' has recently been reviewed and their usefulness and validity confirmed in prospective studies on child health (Goldman et al. 1998). The mother/caretaker will be given a simple morbidity calendar to keep daily records of the child's morbidity status. This chart was pre-tested among 11 households in our pilot study in Mizque and the graphical illustrations proved culturally valid. The number of bowel movements (from sunrise to sunset), color and consistency of the stool as well as specific symptomatic features of the diarrheal episode were recorded using colored stickers (Appendix J). The usefulness of the tools for monitoring child health has been taken up enthusiastically by mothers and quantitative data on diarrhea frequency were collected (Jul-Aug.2002) in one village.
- 2.) Weekly home visits by community-based fieldworkers. Specific inquiries about the occurrence of a diarrheal episode using a standardized questionnaire will be made at the time of the fieldworker's weekly home visit. We will use vernacular terms of locally defined diarrheal illnesses derived from ethnographic pilot investigations in Mizque. For each of those illnesses, we will assess indicators for diarrhea as objectively as possible. This includes frequency of bowel movements and the presence of other symptoms (fever, vomiting, dehydration). Signs of dehydration will be assessed by both the number of urinations in last 24 hours as well as by capillary refill time. The different outcomes of the study (see below) will, thus be obtained by 52 measurements during the 12 months of follow-up. The assessment of the impact of SODIS on diarrheal morbidity will be obtained from cluster-level (villages) and individual (child) level outcome measures:

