Village-level outcome measures: a *cluster(village)-level incidence rate* will be obtained by dividing the total number of diarrheal episodes in a cluster (village) by the total observation time of the study children in each village. This represents an incidence density measure. Similarly, the *mean number of episodes* of diarrhea per village-cluster will be compared among study groups.

Child-level outcome measures: the *total number of days with diarrhea*, and the *mean duration of diarrhea*, and the *number of visits to a healthcare provider* will be used for a child-level analysis of the intervention effect. The impact of

SODIS in terms of reduction of severe diarrheal episodes with blood, and/or fever or persistent episode (>14 days) will be assessed in a separate analysis.

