#### **D. 11. Ethical Considerations**

All of the communities will be covered by the PCI program in a staggered approach providing the setting of a natural experiment for the study. Thus, every household will have access to the SODIS technology by the end of the program. Each village will be informed about the date of the forthcoming implementation of the SODIS intervention, i.e. villages in the control arm of the trial will know and have agreed upon their "delayed-intervention" status. Compensatory actions or resentful demoralization due to differential treatment of intervention and control villages are thus not an issue of concern. The selected communities will be informed through their village government who meet regularly with the PCI representatives, about the background of the study in broad terms. The village government as well as the community representatives must have given their consent for the whole project. Children will be enrolled in the study following written informed consent of both of their parents (Appendix M). Withdrawal from the trial is possible at any time without any consequences for the child, family and household. All information obtained from the questionnaires will be treated as strictly confidential and will not be passed to any other person or institution outside the research team. All children identified during any survey as suffering from a severe form of diarrhea (fever and/or signs of dehydration present) will be referred to the nearest health facility. Health service delivery to the study participant is provided through the regular health care system. Treatment is provided free of charge and is organized through the office of the District Medical Officer (DMO) together with the district health team. The project team is not involved in any patient

care. However, as services of local health posts are often interrupted due to delayed or inadequate supply of drugs our project will make budgetary provisions to support the local health posts in the project area to ensure these services to the study participants.

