An important component of this research is the collection of microbiological testing of stool specimen from study children with appropriate consent. These specimen will be tested for common causes of gastrointestinal illness due to viruses, bacteria and parasites. Stool specimens will be collected at baseline from about 30% of the under five population (approx. 250 samples) in the participating villages and later during the study from about another 250 symptomatic cases with a diarrheal episodes. Field staff will distribute stool collection kits in the morning and collect them in the evening from the households if the child cannot produce a sample at the time of the visit. They will store the

specimen and transport them to the local research office from where they are transferred to the central laboratory (LABIMED) in Cochabamba. The nurse of the local health facility will be notified about the test results, and he/she will then contact the participant and initiate treatment upon a consultation at the health facility.

Water quality monitoring constitutes the second important component. Water samples of stored and SODIS-treated drinking water (in intervention arm) will be collected from about 10 households in every community (about 30% of the study sample) every two months. In addition samples of the raw water sources reported to supply the households with drinking water will be tested. All households will have consented to water quality monitoring of household drinking water.

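### The provider-visit secondary outcome can count visits prompted by the study itself; stool-result call-ins would pull its between-arm ratio modestly toward 1

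*Protocol*

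**What the plan says.** Section D.5 includes among the child-level secondary outcomes "the number of visits to health care providers caused by the diarrhea". Section D.6.c names the same outcome as the "number of visits to a healthcare provider", with no restriction to diarrhea, and says that it "will be used for a child-level analysis of the intervention effect".

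Two study procedures, applied in both arms, can create such visits:

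- **Referral.** Fieldworkers visit weekly and ask about fever and other symptoms. D.6.c adds: "Signs of dehydration will be assessed by both the number of urinations in last 24 hours as well as by capillary refill time". D.11 then states: "All children identified during any survey as suffering from a severe form of diarrhea (fever and/or signs of dehydration present) will be referred". The destination is the closest health facility.
- **Stool results.** A subsample of 220 children (ten per village, so 110 per arm) gives specimens at baseline, at the first diarrheal episode and at six months (D.1, D.5, D.6.b). E.5 says: "The nurse of the local health facility will be notified about the test results, and he/she will then contact the participant and initiate treatment" following a consultation at the facility. D.6.g instead has the study team inform participants, with treatment after consulting the medical center.

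D.11 also says that treatment is free within the regular health system and that the project will budget for support to local health posts.

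**The concern.** A count of provider visits is naturally read as a consequence of illness that SODIS might reduce. If part of the count comes from the study's own testing, that part follows the sampling schedule and not the amount of diarrhea. Each sampled child gives one first-episode specimen, whether the child has one episode or six. A component of nearly equal size in both arms moves the ratio toward 1 and understates a real reduction. Visits added by surveillance also raise the absolute level, so the level does not describe what would happen without the study.

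The costing is exposed too. D.6.e takes household costs of care, transport and visit time from a sample of acute and persistent or severe episodes, and says that research costs are left out. Households' costs for visits that the study prompted would enter unless those visits can be identified.

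The issue belongs in the protocol and its forms. If the origin of a visit is not recorded when it is reported, no later analysis plan can recover it.

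**Working it through.** **The plan's own figures.** The protocol gives no expected number of visits. Its sample size rests on episodes and is unaffected. With the D.8 formula, 5 versus 3.333 episodes per child-year, 10 person-years per cluster and k = 0.2:

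c = 2 + (1.96 + 0.84)² × {8.333/10 + 0.04 × (25 + 11.11)} / 2.778 = 8.43, rounded up to the stated 9 villages per arm.

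**Inputs for the illustration**

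- From the protocol: 330 children per arm; 5 versus 3.33 episodes per child-year (D.8); 110 stool-sampled children per arm.
- Assumed: families seek care for 10% or 20% of episodes. The protocol gives no such rate.
- Assumed: 28% to 49% of first-episode results are positive. The lower value matches the bacterial prevalence in diarrheal cases from a Bolivian community study cited in B.4. The upper value is the parasite prevalence among all tested pilot children (36/74, C.1). Neither is an estimate for first episodes in this trial.
- Assumed: each positive result produces one counted visit, additional to any visit the family made for that episode, and positivity is the same in both arms.

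**Step 1: children with a first episode within 12 months** (Poisson, every child in an arm at the same rate)

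- Control: 1 − e^(−5) = 0.993; × 110 = about 109.
- Intervention: 1 − e^(−3.333) = 0.964; × 110 = about 106.

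The number of call-in opportunities is thus almost the same in both arms, although the episode rates differ by a third.

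**Step 2: family-initiated visits**

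- At 10%: 330 × 5 × 0.10 = 165 versus 330 × 3.333 × 0.10 = 110.
- At 20%: 330 versus 220.
- Ratio in both cases 0.667, a 33% reduction.

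**Step 3: add first-episode call-ins**, with p the share of positive results

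| Care sought | Formula | p = 0.28 | p = 0.49 |
|---|---|---|---|
| 10% | (110 + 106p)/(165 + 109p) | 0.714 | 0.741 |
| 20% | (220 + 106p)/(330 + 109p) | 0.693 | 0.709 |

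The apparent reduction is 26-29% at 10% care-seeking and 29-31% at 20%.

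**Step 4: the wording in D.6.c.** Without the diarrhea qualifier, call-ins for positive six-month specimens can count as well. Adding 110 tests per arm at the same positivity and 10% care-seeking gives (110 + 216p)/(165 + 219p) = 0.753 to 0.793, a 21-25% reduction.

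**Step 5: referrals.** If a constant share s of episodes is referred, the added visits are 330 × 5 × s versus 330 × 3.333 × s. Their own ratio is 0.667 whatever s is. They raise both totals and leave the contrast where it was.

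**The case against.** The strongest reply is that a visit after referral for severe diarrhea is still a visit due to diarrhea, made in both arms under the same rule. That stands. A reader might infer from the two routes that all study-prompted visits bias the ratio toward 1; step 5 shows that this does not follow for referrals. A reader might also infer that the outcome no longer measures the effect of SODIS on care-seeking. The protocol never calls the outcome care-seeking. It lists it beside days with diarrhea and mean duration, and the illustration shows a diluted effect, not a lost one.

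Free treatment cannot be charged to the study either, since D.11 places it in the regular health system, and support for health posts is not arm-specific.

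The size is also open to challenge:

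- The care-seeking rates are not in the documents.
- The 49% comes mostly from children without diarrhea, and C.1 reports parasites less often in symptomatic children.
- Not every positive child need attend, and some call-ins would replace a visit the family made anyway.
- In the pilot none of the 21 children aged 36 months or more had diarrhea, and the stool sample takes two children from each one-year age group. Fewer children than computed may reach a first episode, and their call-ins would then follow the episode rate more closely.
- Under the D.6.g account of result notification a visit by the child is not certain. D.6.g and E.5 need to be reconciled.

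Most of these points make the dilution smaller; none removes the mechanism.

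Finally, counting only family-initiated visits would have its own defect. Weekly referral can pre-empt visits that families would have made, especially for severe episodes. This argues against that restriction, and the fix below does not adopt it. The questionnaires in Appendix J are not shown and may already ask why a visit was made, but the outcome definition makes no use of it.

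**Conclusion.** The point holds as a modest weakness in the definition of one secondary outcome. The protocol lets visits prompted by the study count, does not separate them, and defines the outcome differently in D.5 and D.6.c. Only the stool-result call-ins dilute the between-arm ratio. Under the stated assumptions a true 33% reduction would appear as about 26-31%, or 21-25% if six-month call-ins also count and families seek care for 10% of episodes. Referrals raise the level in both arms without necessarily changing the ratio. These figures illustrate direction and order of size; they rest on assumed care-seeking and positivity rates and on Poisson episodes at a common rate. The primary outcome, the sample size and the other secondary outcomes are untouched.

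**What to change.** Leave referral, result notification and treatment unchanged. Then:

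1. Add one item to the weekly form: was each provider visit the family's own decision, a fieldworker referral, or a call-in after a stool result?
2. Use the same definition in D.5 and D.6.c, restricted in both to visits due to diarrhea.
3. Exclude stool-result call-ins from the outcome.
4. Keep total diarrhea-related visits as the outcome, and report family-initiated and referred visits separately by arm as a sensitivity analysis.
5. Apply the same flag to the household costs in D.6.e, so that costs of study-prompted visits can be identified.

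The cost is one form item and a line in the definition. The limitation is that caregivers report visit origin in an open trial, so the split between family-initiated and referred visits may itself be affected by knowledge of the arm. This is a further reason to keep the total as the outcome and to use the split only as a sensitivity analysis.
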